### Analysis

Descriptive techniques will be used to characterise the patients participating in the study. Data of the effect evaluation will be analysed according to the intention-to-treat and per-protocol principles. Differences between the intervention and control groups with regard to the primary and secondary outcome variables at the follow-up assessments will be analysed with multivariate techniques adjusting for possible differences in baseline scores and background characteristics. Intervention group patients will be included in the per-protocol analysis if they have attended at least four of the six programme sessions.

Data of the process evaluation will be analysed for patients and leaders by means of descriptive analysis.

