## Methods/Design

### Design

This evaluation study is designed as a two-group randomised controlled trial in which patients are randomly allocated to the intervention or control group (the latter receiving usual care). Data are collected at baseline before the start of the intervention, immediately after the programme (six weeks after the start), and six and twelve months after the start of the programme (see figure 1). Data are gathered by means of self-administered questionnaires and telephone interviews. Various measures are taken to ensure blinding in the data collection process. Questionnaires are collected anonymously and sorted by number. The telephone interviews are conducted independently by trained interviewers, who are unaware to which group patients have been allocated.

For practical reasons, the study consists of eleven consecutive cycles, with one or more CDSMP classes in each cycle. In each cycle, patients are included and randomly allocated to the intervention group or control group. The first cycle started in July 2004 and the final one in September 2005. A total of 21 CDSMP classes (with a parallel control group) were conducted in the period October 2004 – January 2006, in six hospitals. At least two CDSMP classes were conducted in each participating hospital (range 2–6). The Medical Ethics Committee of Maastricht University/University Hospital Maastricht granted approval to conduct this trial. Furthermore, local feasibility of the study design was assessed by each of the local Medical Ethics Committees in the other five participating hospitals.

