### Randomisation

In each cycle, patients were randomised after completion of the baseline measurement if a sufficiently large group of eligible patients per hospital could be formed. We decided that at least eight patients per group had to be allocated to the intervention group, because CDSMP classes normally consist of at least eight participants, for reasons of group dynamics [16]. Eligible patients therefore had a slightly higher chance to be allocated to the intervention group (59%) than to the control group (41%) during the total recruitment period. The maximum number of patients allocated to each CDSMP class was set at 14. The randomisation procedure was performed by an independent researcher by random computerised allocation using SPSS 12.0 for Windows.

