In four of the six hospitals, CHF nurse specialists and CHF patients were trained as leaders. These leaders also conducted CDSMP classes in the two other participating hospitals. A total of twelve professionals and eleven CHF patients received four days of training with the CDSMP protocol in the period April 2004 – November 2005. Four of the twelve professional leaders and two of the eleven peer leaders did not implement the programme in the intervention period, due to work, health, or private issues. Each of the groups in which the leaders were trained (n = 4 to 6) included both professional leaders and peer leaders, who practised together, to provide an optimal training situation. The leader training was provided by one of the researchers ([name]) and a CHF nurse specialist of the University Hospital Maastricht in the Netherlands. Both had been instructed as master trainers at Stanford University by Lorig and colleagues in March 2004. The nurse master trainer also conducted several classes in the intervention period.

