### Power calculation

The sample size calculation was based on figures derived from Dutch research among newly diagnosed older CHF patients [21] relating to one of the primary outcome variables in the present study, general self-efficacy expectancies (GSES by Sherer and colleagues [20]). To detect a mean difference of at least 4.0 points in general self-efficacy expectancies between the intervention and control groups (SD = 11.8; equivalent to an effect size of 0.34), at least 137 patients in both the intervention and control groups were required to achieve a power of 80% at an alpha of 0.05 (one-sided). Assuming a drop-out rate of 30% during the trial, a total of 2× 180 patients have to be included in the study.

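### The sample size makes no allowance for delivery in classes and the stated analysis names no class term; run as described, it gives standard errors that are too small for any positive class correlation

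*Protocol article*

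**What the plan says.** All references are to the protocol article.

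- **Delivery.** The Design section reports: "A total of 21 CDSMP classes (with a parallel control group) were conducted in the period October 2004 – January 2006, in six hospitals". Control patients received usual care. The Randomisation section sets a minimum of eight allocated patients per class because "CDSMP classes normally consist of at least eight participants, for reasons of group dynamics", and a maximum of 14. It also says that allocation took place per hospital within each cycle.
- **Leaders.** The Intervention section reports twelve trained professionals and eleven trained peers, of whom: "Four of the twelve professional leaders and two of the eleven peer leaders did not implement the programme in the intervention period". Leaders from four hospitals also served the other two, and the nurse master trainer ran several classes. Group support and modelling are named among the means by which the programme works.
- **Sample size.** The Power calculation section sets the target as "To detect a mean difference of at least 4.0 points in general self-efficacy expectancies", with "SD = 11.8; equivalent to an effect size of 0.34". It concludes that "at least 137 patients in both the intervention and control groups were required" "to achieve a power of 80% at an alpha of 0.05 (one-sided". No class size, intraclass correlation (ICC) or design effect appears.
- **Analysis.** Group comparisons at follow-up "will be analysed with multivariate techniques adjusting for possible differences in baseline scores and background characteristics". No term for class, leader, hospital or cycle is mentioned.

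**The concern.** Patients were randomised individually, but one arm was then treated in groups. Patients in one class share leaders, peers and sessions, and the primary outcomes (self-efficacy, perceived control, cognitive symptom management) are those the programme is assumed to affect directly. Some positive correlation within class is therefore plausible from the article's own account of the mechanism. Controls have no corresponding grouping by class, so the design is partially nested.

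A model that leaves class out understates the variance of the intervention-arm mean. Confidence intervals become too narrow and the type I error exceeds its nominal level. More patients would not cure that; only the model can. A sample size that leaves class out also overstates power to some degree.

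**Working it through.** **Inputs from the article.** Difference 4.0, SD 11.8, power 80%, alpha 0.05 labelled one-sided, drop-out 30% (Power calculation); 21 classes (Design); 187 and 131 allocated (Progress of the study); 12 − 4 = 8 professional and 11 − 2 = 9 peer leaders who delivered the programme (Intervention). **Assumed, because the article gives none:** class ICC of 0.01, 0.05 or 0.10. The calculations use normal approximations, equal class sizes and the same total variance in both arms.

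**1. Reproduce the stated sample size.** n per arm = 2 × [SD × (z_alpha + z_power) / difference]².
- Two-sided 0.05: 2 × [11.8 × (1.960 + 0.842) / 4.0]² = 136.6, so 137. This matches exactly.
- One-sided 0.05: 2 × [11.8 × (1.645 + 0.842) / 4.0]² gives 108. This does not match.

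The plain independent-patient formula accounts for the whole of 137, so no allowance for clustering is hidden in it. The one-sided label is a separate inconsistency; because of it, results are shown both ways below.

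**2. Standard error and type I error if class is ignored, all 318 analysed.** Mean class size m = 187/21 = 8.90. Design effect in the intervention arm: DE = 1 + (m − 1) × ICC. Ratio of true to naive standard error: r = √[(DE/187 + 1/131) / (1/187 + 1/131)]. Type I error: 2 × [1 − Φ(1.960/r)] two-sided, 1 − Φ(1.645/r) one-sided.

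| Assumed ICC | DE | r | Type I, two-sided | Type I, one-sided |
|---|---|---|---|---|
| 0.01 | 1.079 | 1.016 | 5.4% | 5.3% |
| 0.05 | 1.395 | 1.078 | 6.9% | 6.4% |
| 0.10 | 1.790 | 1.151 | 8.9% | 7.7% |

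If 30% are lost evenly, classes shrink and the effect is smaller: r exceeds 1 by about 1%, 5% and 10%, and two-sided type I error at ICC 0.05 is 6.3%.

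**3. Power with 30% loss.** Evaluable patients: 187 × 0.7 = 130.9 and 131 × 0.7 = 91.7; m = 130.9/21 = 6.23. SE = 11.8 × √(DE/130.9 + 1/91.7); power = Φ(4.0/SE − z_alpha).

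| Assumed ICC | DE | Power, two-sided | Power, one-sided |
|---|---|---|---|
| 0 | 1.000 | 70.2% | 80.1% |
| 0.01 | 1.052 | 69.2% | 79.3% |
| 0.05 | 1.262 | 65.7% | 76.4% |
| 0.10 | 1.523 | 61.7% | 73.0% |

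Two-sided, about 10 points of the shortfall from 80% are present at ICC 0. Clustering at 0.05 costs a further 70.2 − 65.7 = 4.5 points.

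**4. Sample size with the design effect.** n per arm = (DE + 1) × [SD × (z_alpha + z_power) / difference]², with m = 8.90 and ICC 0.01, 0.05 and 0.10: 143, 164 and 191 two-sided; 112, 129 and 151 one-sided.

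**5. Leader as the cluster.** If patients divide equally among 8 professional leaders, m = 187/8 = 23.4. For an assumed leader-level ICC of 0.01 to 0.05, DE is 1.22 to 2.12, r is 1.045 to 1.209, and two-sided type I error is 6.1% to 10.5%. With 9 leaders, the upper figure is about 9.9%.

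**The case against.** The strongest objection is that the article never says patients are treated as independent. A reader might infer that the trial's standard errors are definitely too small. The text does not support that: the model is left open, a class effect is neither planned nor excluded, and random-effects detail is commonly placed in an analysis plan, which is not shown here. This stands, and the point about the analysis is therefore conditional. It does not remove the point, because the sample size demonstrably omits clustering and the article does state an adjustment set in which class has no place.

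Second, no ICC is documented. At 0.01 the effect is minor. Allocated patients who attended few sessions also share less of the group experience, which could lower the correlation in the intention-to-treat set. This stands as a limit on the size.

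Third, a reader might infer that clustering brings power down from 80% to about 66%. It does not: two-sided power is already 70% without clustering, because of the small control arm and the drop-out. Nor is the planned power necessarily missed on the article's own label. With 137 evaluable per arm in 21 classes, one-sided power is still about 80% at ICC 0.10.

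Fourth, the leader-level figure of 10.5% is close to a worst case. It supposes equal caseloads, correlation shared across all of a leader's separate classes, and eight professionals only, although the nurse master trainer also led classes. The article gives no caseloads.

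Finally, enrolment has closed, so a design effect can no longer change the sample size. That is correct, but the model can still be settled.

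**Conclusion.** The concern holds in conditional form. Clustering by class exists in the intervention arm, the sample size ignores it, and an analysis carried out as described would give standard errors that are too small for any positive class ICC. Over the assumed range of 0.01 to 0.10, the true standard error is about 2% to 15% above the naive one, with type I error of 5.4% to 8.9% two-sided or 5.3% to 7.7% one-sided. The main consequence is for the validity of intervals and p-values. The loss of power due to clustering is secondary: about 4 to 5 points two-sided and about 4 points one-sided, at ICC 0.05 with 30% loss. All sizes rest on the assumed ICC and on roughly equal classes. This should be fixed; confidence is moderate, since the ICC and the full model are unknown.

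**What to change.** Follow-up was still being collected when the article was written, so the model can be stated before outcome analysis. In the Analysis section, specify for each outcome:

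- a partially nested mixed model with a random class effect in the intervention arm only and separate residual variances by arm;
- terms for hospital and cycle, within which patients were randomised. Without them, a class effect set against ungrouped controls would absorb site and period variation;
- small-sample degrees of freedom (Satterthwaite or Kenward-Roger), as there are only 21 classes;
- a sensitivity analysis with the professional leader as the cluster;
- reporting of the estimated class ICC.

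The Progress of the study section already foresees revisiting the power once drop-out is known; include the class design effect in that restatement, and state which sidedness applies.

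The cost is wording and some programming, plus class and leader identifiers that running the classes should already have produced. The drawback is slightly wider confidence intervals. If the ICC proves close to zero, little is lost.

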**Methods/Design:**

The programme is being evaluated in a two-group randomised controlled trial. Patients were eligible if they had been diagnosed with CHF and experienced slight to marked limitation of physical activity. They were selected from the Heart Failure and/or Cardiology Outpatient Clinics of six hospitals. Eligible patients underwent a baseline assessment and were subsequently allocated to the intervention or control group. Patients allocated to the intervention group were invited to attend the self-management programme consisting of six weekly sessions, led by a CHF nurse specialist and a CHF patient. Those allocated to the control group received care as usual. Follow-up measurements are being carried out immediately after the intervention period, and six and twelve months after the start of the intervention.

An effect evaluation and a process evaluation are being conducted. The primary outcomes of the effect evaluation are self-efficacy expectancies, perceived control, and cognitive symptom management. The secondary outcome measures are smoking and drinking behaviour, Body Mass Index (BMI), physical activity level, self-care behaviour, health-related quality of life, perceived autonomy, symptoms of anxiety and depression, and health care utilisation. The programme's feasibility is assessed by measuring compliance with the protocol, patients' attendance and adherence, and the opinions about the programme.

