### Measurements in the process evaluation

To determine the feasibility of the programme, four process outcomes were assessed by means of structured evaluation forms: (1) the extent to which the programme was performed according to protocol and the time spent on the sessions, (2) patients' attendance, (3) overall patient adherence and specific adherence with regard to homework assignments, and (4) the opinions of the patients and leaders about the programme. Table 3 presents the outcome variables of the process evaluation.

With regard to compliance with the protocol, the leaders recorded after each session whether they had exceeded specified time limits per activity, skipped, shortened or added parts to activities, or used different training techniques than specified in the protocol. In addition, they recorded preparation time, travel time, time spent on the session, and activities resulting from the session (e.g. answering patients' questions afterwards)

The leaders reported on patient attendance and adherence at group level. Absent patients were phoned by the professional leader to ask for the reason of their absence. Overall adherence (i.e. patients' efforts during the programme sessions) was also assessed at group level, using a 5-point scale (very good – very poor). After completing the programme, both leaders and patients reported on the adherence with regard to homework assignments (e.g. drawing up weekly action plans).

Immediately after the programme, patients who had attended at least three of the six sessions received a structured evaluation form to assess their opinion about the CDSMP. They were asked to what extent they had benefited from the programme (5-point scale; not benefited – benefited very much), and which parts they did or did not appreciate. In addition, patients were asked: (1) to give report marks for the quality of the professional leader and the peer leader, and the programme itself (10-point scale; 1 to 10), (2) whether they would recommend the CDSMP to other CHF patients or to patients with other chronic diseases (e.g. diabetes mellitus), and (3) whether the programme had helped them improve specific health behaviours and coping strategies, compared with the situation before they attended the programme. Finally, the patients were asked to suggest improvements to the CDSMP.

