## Discussion

### Progress of the study

Between July 2004 and November 2005, a total of 717 eligible patients were selected for inclusion from six Heart Failure and/or Cardiology Outpatient Clinics, 339 of whom (47.3%) signed the informed consent form and underwent the baseline assessment (see figure 2). The remaining 378 patients refused or were unable to participate in the study for various reasons: for example, 84 patients did not participate because of physical health problems, 74 patients were not interested or felt no need to participate, and another 74 patients had no time or opportunity to participate (see figure 2). After completion of the baseline assessment, 318 patients were included in the trial; 187 patients were allocated to the intervention group and 131 to the control group.

We had calculated that the study would require a sample size of 2 × 180, including a 30% drop-out rate. A total of 187 patients were allocated to the intervention group, which was according to plan. The number of patients allocated to the control group (n = 131), however, was smaller than planned. At present, follow-up data are being collected. The exact drop-out rate and related consequences for the power calculation will become clear after completion of the data collection in January 2007.

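### The per-protocol rule selects on attendance in the intervention arm only, so that comparison is open to selection bias which the planned covariate adjustment cannot fully remove

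*Protocol article*

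**What the plan says.** The Analysis section of the protocol article names two principles in one sentence: "Data of the effect evaluation will be analysed according to the intention-to-treat and per-protocol principles". It then gives the only per-protocol rule in the document: "Intervention group patients will be included in the per-protocol analysis if they have attended at least four of the six programme sessions". No per-protocol rule is given for controls. The abstract describes their condition: "Those allocated to the control group received care as usual". Both analyses are to use "multivariate techniques adjusting for possible differences in baseline scores and background characteristics". The section on the progress of the study reports that "187 patients were allocated to the intervention group and 131 to the control group". The Power calculation section sets the scale for judging any bias: a 4.0-point difference on the general self-efficacy scale, with an SD of 11.8.

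**The concern.** Attending four or more of six weekly sessions is something patients do after allocation, and it may depend on health and motivation. The article itself describes heart failure as prone to sudden worsening and intercurrent illness. Its main outcome, self-efficacy, is the belief that one can carry out intended behaviour, which is close to what keeps a person attending a class.

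The rule removes low attenders from the intervention arm. Their counterparts in the control arm, who would also have missed sessions had they been invited, cannot be identified and stay in. The two groups can then differ in prognosis even if the programme does nothing. At stake is whether the per-protocol estimate can be read as an effect of the programme in those who took it up. As specified, it mixes that effect with the difference between people who attend and people who do not.

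**Working it through.** **Inputs from the article.** Target difference 4.0 points and SD 11.8 (Power calculation); 187 intervention and 131 control patients (Progress of the study). These agree with the article's own derived figures: 4.0 / 11.8 = 0.339, stated as 0.34; and 187 / 318 = 58.8%, stated as 59% in the Randomisation section.

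**Inputs the article does not give (assumed).** L, the share of the intervention arm attending fewer than four sessions: 15-35%. G, the amount in SD units by which low attenders would score worse than attenders without the programme: 0.2-0.4.

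**Bias when the programme has no effect.** Let A be the mean of would-be attenders and N that of would-be low attenders. The undivided control mean is (1 - L) x A + L x N. The per-protocol contrast is A minus this, which is L x (A - N) = L x G x 11.8.

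| L | G | Bias (points) | Share of 4.0 |
|---|---|---|---|
| 0.15 | 0.2 | 0.15 x 0.2 x 11.8 = 0.35 | 9% |
| 0.25 | 0.3 | 0.25 x 0.3 x 11.8 = 0.89 | 22% |
| 0.35 | 0.4 | 0.35 x 0.4 x 11.8 = 1.65 | 41% |

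If low attenders would have scored better by the same gap, the figures become -0.35, -0.89 and -1.65.

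**Effect on the false-positive rate.** With full follow-up and no adjustment, SE = 11.8 x sqrt(1 / (187 x (1 - L)) + 1 / 131). In the middle case this is 11.8 x sqrt(1 / 140.25 + 1 / 131) = 1.43. The one-sided rate is 1 - Phi(1.645 - bias / SE). The two-sided rate uses 1.96 and adds the opposite tail.

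| Case | SE | One-sided 0.05 | Two-sided 0.05 |
|---|---|---|---|
| Low | 1.39 | 8% | 6% |
| Middle | 1.43 | 15% | 9% |
| High | 1.49 | 30% | 20% |

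Both versions are shown because the article states a one-sided alpha, while its 137 per group reproduces only with a two-sided test (one-sided gives 108). That is a separate matter and does not affect this point. With the sign of G reversed, the one-sided rate falls below 5%.

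**Adjustment.** These are unadjusted figures. Under the planned model, G is the gap that remains after adjustment for baseline score and background characteristics, so the bias of the planned analysis is smaller by an amount the article does not allow one to compute. Motivation that was not measured, and illness arising during the six weeks of the programme, are not captured by baseline covariates.

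**The alternative.** A complier average causal effect is, in its simplest form, the intention-to-treat difference divided by the share complying. If the programme has no effect, the intention-to-treat difference is centred on zero and so is this estimate, whatever L and G are. Its SE is roughly the intention-to-treat SE divided by (1 - L): 11.8 x sqrt(1 / 187 + 1 / 131) = 1.34, and 1.34 / 0.75 = 1.79 in the middle case, against 1.43 for per-protocol. The interval is therefore about 25% wider (14% and 39% wider in the low and high cases).

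**The case against.** **Equal standing and choice of result.** A reader might infer that the two analyses have equal standing and that the favourable one could be chosen. The article does not say this. Intention-to-treat is named first, the four-session cut-off was published while follow-up was still running, and a full protocol or analysis plan that is not shown may rank them. The lack of a ranking in an article is therefore not a fault in itself. This stands, but it does not touch the one-arm rule, which the article states.

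**The comparator.** That all controls form the comparison group is an inference. It is the plain reading, since an attendance rule cannot apply to people who have no sessions, but it is not written down.

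**Direction.** It is tempting to say that the rule favours the programme. The article has no data on who misses sessions. The nearest evidence, the reasons for not taking part before randomisation, is mixed: 84 patients had physical health problems, 74 were not interested or felt no need, and 74 had no time or opportunity. Patients who feel no need or are busy could have higher self-efficacy, which would reverse the bias. This stands.

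**Adjustment.** Baseline scores are adjusted for, and co-morbidity, cognitive status and socio-demographics are measured at baseline. This lowers the likely size of the bias without removing it.

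**Attendance data.** The section on the process evaluation says "The leaders reported on patient attendance and adherence at group level", and a reader might infer that the four-session rule cannot be applied to individuals. The same section rules that out: absent patients were telephoned about the reason, and evaluation forms went only to patients who had attended at least three sessions. Attendance per patient must have been known.

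**The alternative has its own assumption.** With a four-session cut-off, a complier analysis assumes no effect in patients attending one to three sessions. They received part of the programme, and those at the first session also received the reference book. If they benefit, the estimate is biased upwards. This stands and shapes the fix.

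**Conclusion.** The concern holds in a limited form. The article specifies an estimator that selects on post-randomisation behaviour in one arm, and the planned adjustment cannot be relied on to restore comparability. Under the stated assumptions the unadjusted bias is about 0.35-1.65 points, or 9-41% of the 4.0-point target. The adjusted bias would be smaller by an unknown amount. Bias towards benefit is plausible but not established. The size rests entirely on assumed attendance and an assumed prognostic gap. The intention-to-treat comparison is planned and is not affected by this rule, so the trial is not invalidated. The point is worth acting on because an estimator that keeps the randomised comparison can be computed from data already held.

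**What to change.** State that conclusions about effectiveness rest on the intention-to-treat analysis and that any adherence analysis is supportive.

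For the adherence analysis, estimate a complier average causal effect with random allocation as the instrument and the same covariates, instead of the one-arm per-protocol comparison or at least beside it. The design suits this, since allocation is random and no control access to the classes is described. Define compliance as any attendance, or keep the four-session cut-off and report the any-attendance definition as a sensitivity analysis. If the per-protocol comparison is kept, state which controls it uses and that randomisation does not protect it.

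The cost is a change of wording and one further model, with no new data; follow-up was still being collected when the article was written. The downsides are a wider confidence interval than per-protocol gives and an exclusion-restriction assumption. With any attendance as the definition, that assumption is only that allocation has no effect on patients who attend no session, which is easier to defend than no effect in those attending one to three.
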